## Abstract

**Background::**

Hemiplegic shoulder pain (HSP) is a frequent complication after stroke and limits patients’ physical functioning of the affected arm, thus compromising their quality of life. Fu's subcutaneous needling (FSN) has been widely applied in the treatment of pain diseases in China; however, its efficacy and safety for HSP remain to be elucidated. We therefore conducted a randomized, controlled trial to summarize the current evidence on the effects of FSN on the recovery outcomes of stroke survivors with HSP.

**Methods::**

Here, we conduct a study design and protocol of a randomized, blinded, controlled study to evaluate the efficacy and safety of FSN in patients with HSP. A total of 60 patients with numerical rating scale (NRS) score above 1 will be recruited in the trial and randomized into FSN group or usual care (UC) group. Patients in the FSN group will receive FSN treatment combined with UC treatment while patients in the UC group will receive UC treatment alone for 4 weeks. The primary outcomes are changes of NRS at baseline, after the 1st treatment, after the final treatment and 4 weeks after the final treatment. Secondary measurements will be changes of Fugl–Meyer score, constant score, MPQ-SF score, quality of life score, and range of motion at baseline, after the final treatment, and 4 weeks after the final treatment. The safety will also be assessed by monitoring the incidence of adverse events and changes in vital signs during the study.

**Discussion::**

Results from this trial will significantly support the application of FSN in the recovery of patients with HSP. If found to be effective and safe, FSN will be a valuable complementary option for patients with HSP.

**Trial registration::**

Chinese Clinical Trial Registry: ChiCTR1900021644 (registered on March 2, 2019).

## Introduction

1

Hemiplegic shoulder pain (HSP) is a common and disabling complication among stroke survivors, with the rate of occurrence ranges from 16% to 84%.^[1–3]^ HSP may negatively affects patients’ range of motion (ROM) and motor functioning, thus withdraw rehabilitation programs and increase duration of hospitalization.^[4]^ Majority of factors may contribute to the occurrence of HSP, such as weakness of the rotator cuff muscles, subluxation, tendon inflammation, and shoulder–hand syndrome.

Accordingly, numerous treatment methods have been suggested, including percutaneous neuromuscular electrical stimulation (NMES), stretching exercises, pharmacologic therapy, shoulder positioning, strapping and taping, intraarticular corticosteroid injections, and so on. Nevertheless, inconclusive evidence was shown for the effectiveness of shoulder taping in reducing HSP.^[5–7]^ Manual techniques such as stretching, positioning, ROM functioning, or massage likely promote comfort only due to the lack of empirical evidence for their effects. Although corticosteroid injections may give satisfactory results, potential side effects include postinjection flare and tendon rupture.^[8]^ Percutaneous NMES requires invasive procedures to implant electrodes and poses the risk of electrode-related infections, which makes clinical implementation difficult.^[9,10]^

Acupuncture is an important component of traditional Chinese medicine and has been widely used in various diseases during the past 1000s of years in China. Many trials had explored the effect and safety of acupuncture for treating HSP,^[11–15]^ and a recent systematic review also concluded that conventional and electroacupuncture could be effective for management of HSP after stroke; however, very high potential for bias should be considered.^[16]^ Fu's subcutaneous needling (FSN) is a new acupuncture therapy, which mainly acts in the subcutaneous layer, like superficial acupuncture documented in “Huangdi Neijing” and developed from Ashi point therapy and wrist-ankle acupuncture therapy.^[17]^ Evidence has indicated that FSN could rapidly relieve the pain and obviously improve the spasm of soft tissues in treating the soft tissues injuries in clinical practice.^[18]^ Some studies had investigated the effect of FSN for HSP in China^[19,20]^; however, most of the trials are of low quality and well-designed randomized controlled clinical trials are still needed.

Thus, we present a study design and protocol of a randomized, blinded, controlled study to assess the efficacy and safety of FSN for treating HSP among stroke survivors. The objective of this study was to determine if FSN could strengthen the effect of usual care (UC) alone. The results of this study are expected to establish an optimal procedure for HSP.

## Methods

2

### Objective

2.1

In this study, the efficacy and safety of FSN combined with UC for HSP versus UC alone will be evaluated.

### Trial design and setting

2.2

This study is a single-center, randomized controlled, assessor-blinded clinical trial which was devised following the Consolidated Standards of Reporting Trials (CONSORT) Statement recommendations^[21]^ and STRICTA.^[22]^ The total study period for this trial is 8 weeks (Fig. 1), including 4-week treatment phase and 4-week follow-up phase.

**Figure 1 F1:**
[figure not shown]
Schedule of enrollment, interventions, and assessments.

The study will commence on June 1, 2019, and will be completed by December 31, 2020, at GuangDong Second Hospital of Traditional Chinese Medicine. Sixty patients who meet the eligibility criteria and sign an informed consent form will be randomly divided into 2 groups to receive either FSN combined with UC or UC treatment alone in a 1:1 ratio. The flowchart of the trial is shown in Figure 2.

**Figure 2 F2:**
[figure not shown]
Flowchart of the study procedure.

## Participants

3

### Recruitment strategies

3.1

Inpatients at acupuncture departments in GuangDong Second Hospital of Traditional Chinese Medicine will be recruited mainly in this RCT. Additionally, posters will be put in the hospitals and a Chinese multipurpose social media named WeChat will be applied to recruit. Brief descriptions of eligible criteria, the free acupuncture treatments and the possible risks of the trial will be marked and all patients have the right to participate or drop out at any time, and will be required to sign the informed consent before the trial begin.

### Eligibility criteria

3.2

The inclusion criteria will be as follows: HPS induced by stroke; Duration ranges from 2 weeks to 6 months at time of recruitment; age ranges from 20 to 80; intensity of HSP evaluated by numerical rating scale (NRS) was above 1; adequate communication ability and intact cognitive function (Mini-Mental Status Examination scores ≥24 points); and signed informed consent.

The exclusion criteria will be as follows: HPS not induced by stroke; combination of heart, liver, or kidney failure endanger the safety of life at any time; younger than 20 years or older than 80 years; those who do not receive acupuncture therapy; women with pregnancy and lactation; participate in other studies; aphasia, and severe cognitive deficits.

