### Outcome measures

3.9

The primary efficacy endpoint will be NRS at baseline, after the 1st treatment, after the final treatment and 4 weeks after the final treatment. The NRS is a segmented numeric version of the visual analog scale (VAS) in which a respondent selects a whole number (0–10 integers) that best reflects the intensity of pain. Thus, we select NRS as the primary measurement to assess the improvement of pain.

Secondary measurements will be as follows:

Fugl–Meyer score: The FMA score consists of 17 items, ranging from 0 to 34, with lower scores demonstrating poorer movement function. In our trial, we just assessed the upper extremity Fugl–Meyer which includes 10 items and ranging from 0 to 20 at baseline, after the final treatment and 4 weeks after the final treatment.

Constant score: A supplementary assessment of function of the shoulder joint will be assessed by the constant score scale at baseline, after the final treatment and 4 weeks after the final treatment.

Short-form of McGill pain questionnaire (MPQ-SF) score: The MPQ-SF is a multidescriptive measure of pain that consists of 22 pain questions. It reveals the nature of shoulder pain. It will be evaluated at baseline, after the final treatment and 4 weeks after the final treatment.

Quality of life (QOL) score: QOL will be evaluated using the Chinese version of EQ-5D-5L^[25]^ at baseline, after the final treatment and 4 weeks after the final treatment.

ROM: Pain-free passive range of motion (PROM) of the shoulder was designated as the ROM attained in the most painful position and was measured using a digital goniometer in 6 directions: flexion, extension, abduction, adduction, external rotation, and internal rotation. Five directions of the shoulder joint were measured (flexion, abduction, adduction, internal rotation, and external rotation), while participants were lying in a supine position. In addition, shoulder extension was measured in the side-lying position. PROM was also evaluated at baseline, after the final treatment and 4 weeks after the final treatment.

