### Sample size calculation

3.12

The trial is designed to determine the role of FSN for treating HSP among stroke survivors. Therefore, NRS change will be used as an evaluation index. According to our previous pilot study, the change of NRS before and after treatment in the treatment group was shown to be 3.40 ± 0.48 (n = 10) and that in control group was 3.10 ± 0.23 (n = 10). Sample size was estimated using the following formula: 

where n represents the number of samples required, n = n_1_ + n_2_, *Q*_1_ = n_1_/n, *Q*_2_ = n_2_/n with a significance level (*α* = 0.05) of a 2-sided 2-sample *t* test and 80% power to detect a difference between the 2 groups. Thus, a total sample size of 60 patients will be recruited allowing for 10% of attrition, with 30 in each.

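### Entry at NRS above 1 admits patients whose largest possible fall is smaller than the mean falls used to size the trial, so the planned 0.30-point contrast may be diluted

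*Protocol article*

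**What the plan says.** - **Entry.** Section 3.2 (Eligibility criteria) sets the pain criterion as "intensity of HSP evaluated by numerical rating scale (NRS) was above 1". The abstract repeats it: "A total of 60 patients with numerical rating scale (NRS) score above 1 will be recruited".
- **Scale.** Section 3.9 (Outcome measures) describes the NRS as one on which the respondent "selects a whole number (0–10 integers) that best reflects the intensity of pain".
- **Sizing.** Section 3.12 states that "NRS change will be used as an evaluation index". The pilot change "in the treatment group was shown to be 3.40 ± 0.48 (n = 10"), and "that in control group was 3.10 ± 0.23 (n = 10"). With two-sided alpha 0.05, 80% power and 10% attrition, the section arrives at 60 patients, 30 per arm.
- **Randomisation and analysis.** Section 3.3 describes random numbers in sealed envelopes and mentions no baseline pain strata. Section 3.13 compares the groups with an independent-sample t test.
- **Time points.** Section 3.9 measures the primary NRS outcome at baseline, after the first treatment, after the final treatment and four weeks later.

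**The concern.** The entry rule and the sample size assumption do not fit together. The NRS cannot go below 0, so the largest possible fall equals the baseline score. At entry scores of 2 and 3 that maximum is below even the mean fall assumed for usual care alone.

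The objective in section 2.1 is an add-on effect: FSN plus usual care against usual care. A patient whom usual care already brings close to 0 leaves little room for FSN to add anything by the end of treatment. The planned difference is only 0.30 points and the power margin is thin, so a modest share of such patients could matter. Neither the randomisation nor the t test, as described, offsets this, and no later analysis plan can change who was enrolled.

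**Working it through.** **Inputs.** Mean falls 3.40 and 3.10, ± values 0.48 and 0.23 read as SDs, alpha 0.05 two-sided, power 80%, attrition 10%, 30 per arm (all section 3.12); NRS in whole numbers 0–10 (section 3.9); entry above 1, so 2 or more (section 3.2). *Assumption:* the share f entering at NRS 2–3 is not in the document and is ranged from 10 to 30%.

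**1. The plan's own figure.** Difference = 3.40 − 3.10 = 0.30. Pooled SD = √((0.48² + 0.23²)/2) = 0.376.
- Normal approximation: n per arm = 2 × (1.960 + 0.842)² × 0.376² / 0.30² = 24.7, so 25; 50 in total; 50/0.9 gives 56.
- Exact t test: 26 per arm; 52/0.9 gives 58. The stated 60 is consistent with this.
- After 10% attrition, 27 per arm remain. The noncentrality is 0.30/(0.376 × √(2/27)) = 2.93, and power is 82%.

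**2. The floor.** If the fall does not depend on baseline except that it cannot exceed it, fall = min(baseline, Normal(mean, SD)). Expected values:

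| Baseline NRS | FSN + UC | UC | Difference |
|---|---|---|---|
| 2 | 2.00 | 2.00 | 0.00 |
| 3 | 2.95 | 2.95 | 0.00 |
| 4 | 3.38 | 3.10 | 0.28 |
| 5 | 3.40 | 3.10 | 0.30 |

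**3. Dilution.** With a contrast of about 0 in a share f, and the other patients far enough from the floor to show the full 0.30, the overall difference is 0.30 × (1 − f). Power is simulated at 27 per arm with a two-sided t test:

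| f (assumed) | Difference | Power, all at NRS 3 | Power, half at 2 and half at 3 |
|---|---|---|---|
| 0% | 0.30 | 82% | 82% |
| 10% | 0.27 | 75% | 57–58% |
| 20% | 0.24 | 65% | 40% |
| 30% | 0.21 | 56% | 28% |

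The two power columns differ because patients capped at 2 also widen the spread. Check at f = 10%, even split: the simulated SDs are 0.555 and 0.325, pooled 0.455; the noncentrality is 0.27/(0.455 × √(2/27)) = 2.18, against a critical value of 2.007, which gives power of about 57%.

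**4. Alternative response model.** If falls are proportional to baseline and 0.30 applies at an assumed mean baseline of 5, the contrast is 0.30 × 2/5 = 0.12 at NRS 2 and 0.30 × 3/5 = 0.18 at NRS 3. It is smaller, but not zero.

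**5. Can the ± values be SDs of patient-level change?** Ten whole-number changes with mean 3.10 have the least spread as nine 3s and one 4, with SD 0.32. With mean 3.40 they have it as six 3s and four 4s, with SD 0.52. The stated 0.23 and 0.48 are both smaller. If they are standard errors, the SDs are 0.23 × √10 = 0.73 and 0.48 × √10 = 1.52. Power at 27 per arm is then only about 15% with no mild patients at all.

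**The case against.** **Broad entry matches the objective.** The trial asks about FSN for hemiplegic shoulder pain, and a higher entry score answers a narrower question. This stands as a reason to leave the choice to the investigators. It does not remove the mismatch with section 3.12.

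**An effect could still show in mild patients.** A reader might infer that no effect can appear at NRS 2–3. The document does not support that. A zero contrast requires the same absolute fall at every baseline, which is nowhere stated; under proportional falls some contrast remains. The primary outcome also includes NRS after the first treatment, when a patient at 2 or 3 may still have room to differ, whereas 3.10 and 3.40 are changes over the whole treatment.

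**The pilot does not contradict the entry rule.** A reader might argue that, with n = 10, no value lies more than (n − 1)/√n = 2.85 SDs from the mean, so every pilot fall was at least 3.10 − 0.23 × 2.846 = 2.45 or 3.40 − 0.48 × 2.846 = 2.03, and no pilot patient began at NRS 2. That needs the ± values to be SDs, which step 5 puts in doubt. Read as standard errors, they give bounds of 1.03 and −0.92, and NRS 2 patients are possible. Even on the SD reading, 20 patients with none at NRS 2 would be compatible with entry above 1.

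**The power figures are fragile.** The share and its split are assumed, the SDs are doubtful, and pilot patients at NRS 3 may already have been limited by the floor, so the cap may be counted twice. This stands. The direction of the effect is firmer than its size.

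**Conclusion.** The point holds as a mismatch between the entry rule and the sizing assumption. Patients at NRS 2–3 are eligible, and their maximum fall is below both assumed mean falls; that part is plain arithmetic on the article's figures. The consequence is conditional. With falls independent of baseline, the end-of-treatment contrast in these patients is about 0 instead of 0.30; with proportional falls it is reduced but present.

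The overall loss depends on a share the document does not give, so the steps in the power table show sensitivity and do not forecast this trial. They also depend on reading the ± values as SDs; if these are standard errors, the variance is the larger problem and power is low with or without mild patients. The findings do not extend to saying that FSN's effect is bound to be missed in mild patients, or that the pilot conflicts with the criterion.

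**What to change.** Before recruitment opens (section 4.1 says it has not begun), reconcile section 3.2 and the abstract with section 3.12 in one of two ways.

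1. **Set an entry score that leaves room for the assumed fall.** Arithmetically this means a score above 3.40. Which score is appropriate is a clinical decision for the investigators. The cost is an amendment to one criterion, a smaller eligible pool, and a conclusion limited to patients with more than mild pain.

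2. **Keep milder patients and plan for them.** Stratify the randomisation by baseline NRS, account for baseline NRS in the primary comparison, and restate the expected difference and power for the population admitted. Adjustment can recover some of the extra spread but does not restore the lost contrast, so the restatement is needed as well. By the normal approximation with the SD held at 0.376 and 10% attrition, totals of 69, 87 and 114 would be needed at 10, 20 and 30% mild patients, against 56 by the same formula with none. Any added spread would raise these totals.

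In either case, state in section 3.12 whether the pilot ± values are SDs or standard errors, and give the pilot baseline NRS distribution, since the restated power depends on both.

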### Randomization and allocation

3.3

Random numbers will be generated by the random number generator in the SPSS statistical software package (Version 20.0, IBM SPSS Statistics, IBM Corp, Somers, NY). Another specified researcher who is not involved in the study was responsible for it.

The allocation of participants will be sealed in a sequentially numbered opaque envelope. If the participant meets the inclusion criteria and signs informed consent, the above specified researcher will sequentially give the sealed random number envelope to the physician, who will open the envelope and allocate the participant to either FSN or UC group according to the random number.

### Blinding

3.4

A single-blinded method will be used. While the participants and practitioners cannot be blinded, we blinded the outcome assessors, data manager, and statistics analyzer. The assessor will be instructed not to communicate with participants about the possibility of their treatment. James et al's blinding index will be evaluated after the completion of the study to evaluate the success of blinding.^[23]^

### Interventions

3.5

In the 4-week treatment phase, participants in both groups will receive UC treatment, and those allocated to the intervention group will also receive FSN treatment.

### UC treatment in both groups

3.6

Both groups underwent identical conventional rehabilitation programs including physical therapy and occupational therapy sessions, each lasting 60 minutes per day for 5 consecutive days per week. Traditional acupuncture therapy will be administered according to individual needs. Details of UC used during the trial will be recorded, noting any change of UC and the reasons.

### FSN add-on treatment in the intervention group

3.7

Patients will also be asked to take a lateral position with the affected limbs upside. For each patient, the positive reaction points (most significant tenderness points) around the affected shoulder will be identified and marked. Insertion points will be located 7 to 8 cm above or inferior to the points. After disinfection with 75% ethanol of each insertion point, a No. 6 disposable FSN needle (Fig. 3) was quickly inserted through the skin and into the subcutaneous layer. It was important to keep the needle tip aligned to the positive reaction point and just touched the muscular layer. Then draw a little back and push the needle forward toward the positive reaction point until the whole soft tube was beneath the skin. The steel needle was then drawed back 3 mm to avoid injuring blood vessels or other tissues during the following procedure. The needles were moved smoothly and rhythmically from one side to another horizontally 200 times in 2 minutes. Meanwhile, we will ask the patient to exercise the involved joints. If it did not make trouble with the movement, the steel needle will be pulled out while the soft tube of the needle remained under the skin for 8 to 24 hours.^[24]^ FSN will be conducted once daily, 5 times a week and lasted for 4 weeks.

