In our trial, strict quality control procedures have been applied to avoid bias, such as randomization and allocation concealment, assessor blinding and adequate sample size. However, methodologic limitations still exist. First, the trial is conducted in a single center. Thus, regional differences cannot be distinguished. Second, all the participants may have a higher expectation of acupuncture therapy because the trial was carried out in hospital of traditional Chinese medicine. Third, the therapists and the participants cannot be blinded in this study due to wide differences between FSN and UC treatment.

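### The tube left near the shoulder in the FSN arm can unmask the assessor of end-of-treatment shoulder measures, and assessor blinding cannot protect the self-rated primary NRS

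*Protocol article*

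**What the plan says.** Protocol article, section 3.4 (Blinding): "While the participants and practitioners cannot be blinded, we blinded the outcome assessors, data manager, and statistics analyzer". To protect the assessor's blind it gives one instruction: "The assessor will be instructed not to communicate with participants about the possibility of their treatment". It also plans a check, in that a "blinding index will be evaluated after the completion of the study to evaluate the success of blinding".

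Section 3.7 (FSN add-on treatment): tender points "around the affected shoulder will be identified and marked", and the needle goes in 7 to 8 cm from them. It is advanced "until the whole soft tube was beneath the skin". If movement is not hindered, the steel part is withdrawn and "the soft tube of the needle remained under the skin for 8 to 24 hours". Sessions are daily, five a week for four weeks. Section 3.5 confines FSN to the intervention arm.

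Section 3.9 (Outcome measures): the primary NRS is a whole number from 0 to 10 picked by the respondent. It is taken at baseline, after the first treatment, after the last treatment and four weeks later. The Constant score and goniometer PROM in six directions are secondary. For the latter, "PROM was also evaluated at baseline, after the final treatment and 4 weeks after the final treatment". No interval between the last session and the assessment is given.

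Section 4 (Discussion) says that "strict quality control procedures have been applied to avoid bias, such as randomization and allocation concealment, assessor blinding", together with sample size. It then lists as limitations that participants are unblinded and may have higher expectations of acupuncture.

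**The concern.** There are two separate problems.

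First, the assessor handles the very shoulder near which, in one arm only, a tube may still be lying. An instruction about conversation does nothing about what is seen or felt in a hands-on examination. An assessor who learns the arm can, without intending to, influence where a pain-free limit is read on the goniometer or how shoulder function is scored.

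Second, for the primary outcome the rater is the patient, and the patient knows the arm. Blinding whoever writes the number down leaves expectation in place. The Discussion names assessor blinding as a bias control, and names unblinded patients and expectation as limitations, but it never says that these limitations fall on the primary endpoint. A reader could take the blinded label, which the Abstract also uses, as covering the main result.

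**Working it through.** **A. Which measures and visits are exposed to the tube (sections 3.5, 3.7 and 3.9)**

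1. Arm: only FSN patients can have a retained tube.
2. Duration: 8 to 24 hours after a session. An assessment more than 24 hours after the last session falls outside this window; one on the same day may fall inside it. The article does not say which applies.
3. After the first treatment: only the NRS is taken. With daily sessions, a rating between sessions one and two probably falls while the tube is in place or just after removal, but the patient is the rater.
4. After the last treatment: PROM and the Constant score are taken. This is the one visit at which the tube can expose assessor-taken measures.
5. Four weeks later: no tube.
6. Protection: the no-discussion instruction is the only preventive step. The blinding index can detect lost blinding but does not prevent it. The article says when the index is evaluated, not when the guesses are collected.

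**B. How a reporting shift in the NRS compares with the planned effect (section 3.12)**

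Inputs: changes of 3.40 (SD 0.48) and 3.10 (SD 0.23), two-sided alpha 0.05, 80% power, 10% attrition, 30 per arm.

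- Planned difference: 3.40 − 3.10 = 0.30.
- Pooled SD: √((0.48² + 0.23²)/2) = √0.14165 = 0.376.
- The plan's own figure: the two-sample t test needs 25.7, so 26 per arm; 26/0.9 = 28.9, so 29 per arm and 58 in total. The stated 60 is reproduced to within two patients.

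An average shift is the share of FSN patients affected times the size of the shift. For an assumed one-point shift:

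- 30% affected: 0.3 × 1 = 0.30, equal to the planned difference.
- 50% affected: 0.5 × 1 = 0.50, and 0.50/0.30 = 1.7 times the planned difference.

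Chance of a significant result with no true effect, 30 × 0.9 = 27 completers per arm, and noncentrality = bias/(SD × √(2/27)):

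| Assumed bias (points) | SD | Noncentrality | Significant |
|---|---|---|---|
| 0.1 | 0.376 (plan) | 0.98 | 16% |
| 0.2 | 0.376 (plan) | 1.95 | 48% |
| 0.3 | 0.376 (plan) | 2.93 | 82% |
| 0.3 | 1.5 to 2.0 (assumed) | 0.73 to 0.55 | 11% to 8% |
| 0.5 | 1.5 to 2.0 (assumed) | 1.22 to 0.92 | 23% to 15% |

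Without bias the figure is 5%. The shares and biases are assumptions, and so are the wider SDs. The table shows how sensitive the comparison is. It is not evidence that bias of this size will occur.

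**The case against.** A reader might infer that the tube reveals the arm of every FSN patient at every post-treatment visit. The documents do not support that. The tube is described as lying wholly under the skin, its retention is conditional, no external part or dressing is described, and the device figure is not available. A puncture mark is not specific to one arm either, because usual care may include traditional acupuncture (section 3.6). These points stand, and they limit the claim to what the tube can do at one visit, for secondary measures.

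It can also be said that hours of assessment and covering of the site are details that an article leaves to the full protocol. This stands in part. But the article itself fixes the tube time, the assessment points, the hands-on measure and the claim of blinding. Taken together these leave a gap that the one stated instruction does not close.

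On the NRS, the authors already disclose unblinded patients and expectation, and the objective is an add-on comparison that does not claim a needle-specific effect. An open add-on design with self-rated pain is a legitimate choice. Assessor blinding is also one of several safeguards listed, and the Discussion does not say outright that it protects the NRS. All of this stands. What is missing is the link between the admitted limitation and the primary endpoint.

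Finally, moving a visit does nothing for self-report bias. That is correct, and the two problems need separate remedies.

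**Conclusion.** The concern holds in a limited form. The retained tube can unmask the assessor of PROM and the Constant score at the end-of-treatment visit, because neither the timing relative to tube removal nor any covering of the site is stated. Whether it does so depends on when patients are seen and whether the tube can be seen or felt, which the article does not settle. The 4-week follow-up is not exposed to the tube.

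That assessor blinding cannot protect the primary NRS follows directly from the text: the patient is the rater and is not blinded.

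The size of either bias cannot be derived from the documents. The sensitivity of the NRS comparison is greatest under the plan's own small difference and SD, and much lower if the SD is 1.5 to 2.0. It would be wrong to read the figures as showing that the trial will give a false positive result. This is a worthwhile, inexpensive improvement and does not invalidate the design.

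**What to change.** FSN treatment stays as it is.

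1. Take the assessor-measured end-of-treatment outcomes on the same fixed day in both arms, after the last tube has been removed. Cover the shoulder area in the same way in both arms at every assessor visit, including the one after the first treatment.
2. Collect the assessor's treatment guess at the end-of-treatment visit and use it for the blinding index already planned.
3. State where the NRS is defined and where results are interpreted that it is an unblinded self-report. Interpret a difference as the effect of adding FSN to usual care, including expectation and extra contact. In the Discussion, restrict assessor blinding as a bias control to the outcomes that the assessor measures.

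The cost is dressings, a shift of about a day for one visit, one extra form item and some wording. Steps 1 and 2 serve the secondary measures; only step 3 addresses the NRS, and it does so by limiting the interpretation, not by removing the bias.
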